### Procedure for unblinding if needed {17b}

Not relevant.

## Data collection and management

### Plans for assessment and collection of outcomes {18a}

Participants will complete primary outcomes (i.e., social anxiety symptoms, relationship, and sexual satisfaction) and secondary outcomes (i.e., dyadic adjustment, closeness, emotion regulation and communication) at pre-treatment, post-treatment, and at 6-month follow-up. In addition, during the intervention, there will be weekly assessments of primary outcomes. Participants’ partners will also complete measures of primary and secondary interpersonal outcomes (relationship satisfaction, sexual satisfaction, dyadic adjustment, relationship closeness, difficulties in interpersonal emotion regulation, and communication) at pre-treatment, post-treatment, and 6-month follow-up.

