### Objectives {7}

The present study aims to adapt and test the efficacy of an iCBT program for adults, namely, the iSOFIE (*The Internet Social Phobia*) [17], a self-help treatment informed by the model of SAD by Clark and Wells [18]. The iSOFIE program has been tested in many trials in Sweden, as well as in other countries like Norway and Romania, where it was found to be effective [19, 20]. Since it was originally developed in Swedish, our first goal concerning this project is to translate and culturally adapt it to European Portuguese, thus originating the PORTiSOFIE (*The Portuguese Internet Social Phobia*).

Our second goal is to test the effect of PORTiSOFIE on the following outcomes:Primary outcomes (SAD symptoms, relationship and sexual satisfaction);Secondary outcomes (dyadic adjustment, closeness, emotion regulation and communication).

For this, we will conduct a controlled study, with the following aims:Dissemination of study and recruitment of potential users;Implementation of PORTiSOFIE and measurement of relevant outcomes;Allocate participants to the groups (intervention vs. attention control group) and assess primary outcomes (i.e., social anxiety symptoms, sexual satisfaction and relationship satisfaction) and secondary outcomes (i.e., dyadic adjustment, closeness, difficulties in interpersonal emotion regulation, and communication) at baseline/pre-treatment;Implementation of PORTiSOFIE with a weekly assessment of the primary outcomes;Assess of primary and secondary outcomes at posttreatment and 6-month follow-up.

The study will expand knowledge on the use of iCBT for adults with SAD in a new cultural context andlanguage. Considering that amorous relationships are usually negatively affected by SAD, we also aim to highlight the role of partners by incorporating relationship dimensions (dyadic adjustment, closeness, emotion regulation and communication). This approach will help to further understand the effect of the intervention on an important interpersonal context.

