## Interventions

### Explanation for the choice of comparators {6b}

Participants in the intervention group will receive PORTiSOFIE treatment. If the intervention in our study shows preliminary efficacy, it will be offered to the control group after the study period.

While the intervention group is undergoing treatment, participants in the wait-list control group (attention group) will be monitored weekly via the iTherapy platform. Each week, participants will be asked to complete a brief symptom self-report instrument focusing on key indicators of social anxiety. The therapist will review the responses and may follow up with a short message or contact to acknowledge receipt and check on general well-being. No therapeutic content or guidance will be provided during this monitoring, in order to preserve the integrity of the control condition while ensuring ethical oversight and participant safety.

To support retention, both groups will receive automated email reminders at important points in the study (e.g., before scheduled assessments or symptom check-ins). These messages will serve to reinforce participant engagement, clarify upcoming steps, and help reduce attrition. Additionally, the weekly contact with a therapist in the control group is designed not only for monitoring purposes but also to foster a sense of continued involvement, reducing the likelihood of dropout.

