### Outcomes {12}

Primary outcomes include social anxiety symptoms and sexual and relationship satisfaction.

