## Assignment of interventions: blinding

### Who will be blinded {17a}

As this is a psychological intervention study, blinding of participants and the online therapist is not feasible. This may introduce performance or expectancy biases, particularly in self-reported outcomes. To mitigate these risks, both groups will receive structured content and regular contact through the platform, reducing differences in attention. As the data analysis will be conducted by members of the research team who are also involved in participant support, blinding during statistical analyses is not possible. However, analyses will be based on pre-specified hypotheses and outcome measures to reduce bias. All procedures and decisions will be transparently reported to enhance the credibility of the findings.

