## Statistical methods

### Statistical methods for primary and secondary outcomes {20a}

Descriptive statistics will be reported using means and standard deviations for continuous variables, and frequencies for categorical variables. Primary analyses will follow the intention-to-treat principle. To assess treatment effects, we will conduct analyses of covariance (ANCOVA) comparing post-intervention scores between the experimental and control groups, while adjusting for baseline levels of the respective outcome variable (e.g., LSAS for social anxiety), as well as for age and relationship duration, which will be included as covariates due to their known associations with treatment outcomes and interpersonal functioning. This approach allows for greater precision in estimating intervention effects and accounts for potential baseline imbalances. Missing data will be addressed using multiple imputation under the assumption of missing at random (MAR), in line with recommendations from meta-analytic research on dropout in CBT trials [29]. A two-tailed significance level of *p* < 0.05 will be used for all hypothesis testing. Effect sizes (Cohen’s *d*) will also be calculated to assess the magnitude of between-group differences, consistent with prior meta-analytic findings on the efficacy of internet-based CBT for social anxiety disorder [30].

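### Weekly measurement appears to differ between arms (primary outcomes alongside PORTiSOFIE, a brief unnamed anxiety form for controls), and the stated attention balance does not fit the control description

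*Protocol article*

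**What the plan says.** Weekly measurement is described in three places in the protocol article.

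- *Objectives {7}* lists, as one step, "Implementation of PORTiSOFIE with a weekly assessment of the primary outcomes".
- *Plans for assessment and collection of outcomes {18a}* says that "during the intervention, there will be weekly assessments of primary outcomes". The sentence names no arm.
- *Explanation for the choice of comparators {6b}* describes the wait-list (attention) arm: "Each week, participants will be asked to complete a brief symptom self-report instrument focusing on key indicators of social anxiety". The therapist reviews the answers and may send a short message, but controls get nothing therapeutic.

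*Outcomes {12}* defines the primary set: "Primary outcomes include social anxiety symptoms and sexual and relationship satisfaction". The instruments are LSAS and SPIN (social anxiety), GMREL (relationship) and GMSEX (sexual).

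*Who will be blinded {17a}* concedes possible performance and expectancy bias and offers as mitigation that "both groups will receive structured content and regular contact through the platform, reducing differences in attention".

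*Statistical methods {20a}* plans "analyses of covariance (ANCOVA) comparing post-intervention scores between the experimental and control groups", adjusted for baseline, age and relationship duration, with multiple imputation under missing at random. It does not say whether weekly scores are used.

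**The concern.** The trial is open and every primary outcome is self-reported. If one arm rates its anxiety, relationship and sex life every week while the other completes a short anxiety form, the post-treatment contrast carries any effect of repeated self-rating along with the effect of therapy. For relationship and sexual satisfaction, no weekly measure is described for controls at all.

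There are two further consequences. Unequal burden could produce unequal dropout, and the protocol expects about 26% dropout overall. Weekly scores are also the natural auxiliary information for imputing a missing post-treatment score. If they are on different instruments, or exist in one arm only, they cannot serve both arms in the same way.

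The blinding section relies on similar content and contact in both arms as its safeguard, so a mismatch with the control description weakens that safeguard.

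**Working it through.** **1. Sections side by side.** The only open question is whether the weekly assessment in {18a} covers one arm or both.

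- *Intervention arm only.* This is the natural reading, because {7} ties the assessment to the programme. The arms then differ in weekly measurement: three outcome domains against one, and possibly different anxiety instruments.
- *Both arms.* {18a} then gives controls weekly relationship and sexual satisfaction ratings, whereas {6b} gives them a brief anxiety form. The sections conflict.

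Either way the text must change.

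**2. Structured content.** The only structured content described is the nine modules in {11a}. Controls do not receive these during the comparison period. They receive a weekly form, possible short messages and reminders. That supports the regular contact claimed in {17a}, but not the structured content.

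**3. Weekly burden, upper bound.** From the instrument descriptions, if every primary instrument were given in full each week: LSAS 24 × 2 = 48; SPIN 16 (Portuguese version); GMREL 5; GMSEX 5.
48 + 16 + 5 + 5 = 74 ratings per week; 74 × 9 = 666 over nine weeks.
The length of the control form is not stated.

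**4. The plan's own figure.** For d = 0.80, two-sided 5% and 80% power, the two-sample t-test needs 25.5, so 26 per group and 52 in total (power 0.807). For dropout, 52 / (1 − 0.26) = 70.3, against the stated 70. The figure reproduces and does not depend on the weekly schedule.

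**5. What a measurement effect would do (assumed sizes).** With 26 per arm and no true effect, suppose unequal measurement alone shifts the contrast by δ SD. The chance of significance in that direction is Φ(δ√(26/2) − 1.96):

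| δ | chance |
|---|---|
| 0 | 2.5% |
| 0.1 | 5% |
| 0.2 | 11% |
| 0.3 | 19% |

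The document gives no value for δ.

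**6. Dropout and imputation (assumed values).** Large simulation, 400,000 per arm; true d = 0.80; correlations baseline–post 0.5, last weekly–post 0.75, baseline–weekly 0.5 to 0.6; log-odds of dropout rising 0.5 to 1.2 per SD of a worse weekly score; regression imputation within arm.

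| Dropout, treated / control | Predictors | d obtained |
|---|---|---|
| 26% / 26%, tied to weekly score in treated arm only | baseline | 0.86–0.93 |
| same | baseline + weekly | 0.80 |
| 35% / 15% | baseline | 0.84–0.97 |
| 26% / 26%, same mechanism in both arms | baseline | about 0.80 |
| same | baseline + weekly in both arms | 0.80 |
| same | weekly used in treated arm only | 0.67–0.75 |

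The last row is the direct argument for a common instrument: using weekly information in one arm only can shift the estimate the other way.

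**7. Precision.** With 26% missing at random, the variance of an arm mean relative to complete data is r² + (1 − r²)/0.74, where r is the correlation of the predictors with the post score. At r = 0.5 this is 1.26; at r = 0.9 it is 1.07. Weaker predictors cost precision, but imputation remains possible.

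**The case against.** The case on the other side is substantial, and much of it stands.

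- *The arm split is inferred.* {18a} names no arm, and its preceding sentence concerns participants generally. This is correct, but the alternative reading turns the issue into a contradiction with {6b} and does not remove it.
- *The endpoint is measured alike.* Both arms complete the same instruments at pre-treatment, post-treatment and 6 months. This stands. What remains is possible reactivity to repeated rating, and attrition.
- *Weekly monitoring could be part of the treatment package.* This is a defensible position, but the protocol does not state it, and it sits badly with an attention control and the claim in {17a}.
- *Imputation does not depend on the weekly data.* A reader might infer that weekly scores which differ by arm make the imputation unworkable. The document does not support that. It never says weekly scores enter the model, the predictor list may properly sit in an analysis plan, imputation can be run by arm, and the control anxiety form could serve as an auxiliary for LSAS and SPIN.
- *The numbers are assumed.* The 74 ratings are an upper bound, since nothing says every instrument is given in full each week. The correlations, slopes and 35% versus 15% split are not in the protocol, which gives one overall dropout rate. {6b} also describes reminders for both arms and weekly therapist contact for controls, partly to limit dropout.
- *{17a} claims only a reduction of differences in attention.* This is fair as regards contact. Its reference to structured content still has no counterpart in {6b}.

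**Conclusion.** The point holds in a limited form. Read together, {7}, {6b} and {18a} either describe different weekly measurement by arm or contradict one another, and {17a} credits controls with structured content that {6b} does not describe. Repeated self-rating may therefore be confounded with treatment, most plainly for relationship and sexual satisfaction, and weekly data cannot be used in a common way across arms.

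The document does not allow the bias to be sized. The simulated d of about 0.84 to 0.97 against a true 0.80 is illustrative. It needs dropout that differs between arms in rate or in mechanism, together with imputation from baseline alone. Bias is about zero when dropout is the same in both arms. A reader should not conclude that the primary endpoint is measured differently between arms, that the sample size is wrong or that imputation fails. The point still deserves action, because the change is small before recruitment (planned from January 2026) and weekly control data that were not collected cannot be recovered later.

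**What to change.** 1. Reconcile {7}, {6b} and {18a}: name one weekly instrument and give it to both arms on the same schedule. A short scale is enough. Keep the full battery at pre-treatment, post-treatment and 6 months.
2. State in {20a} that the weekly scores enter the multiple imputation as auxiliary variables, with imputation run by arm. With about 26 completers expected per arm (35 × 0.74 = 25.9), a few weekly scores or a summary is more workable than all nine.
3. Correct {17a} to say that controls receive monitoring and contact without structured content.

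The cost is form set-up on the platform and some wording. The downside is slightly more burden for controls, or less weekly detail in the intervention arm if the shorter form is chosen. If the sponsor prefers to keep different weekly measurement, the protocol should say so and list it as a limitation. That leaves the confounding in place.

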### Plans to promote participant retention and complete follow-up {18b}

We expect some difficulties associated with sample collection and retention rates during the implementation of the protocol. We will collect a number of participants above the minimum needed, so that dropout does not decrease statistical power. To minimize dropout, participants and their partners will receive encouragement to complete the assessments at each stage. For participants, therapist feedback will also serve to promote continued engagement. For partners, we will provide a short and clear explanation of their role and its relevance to the study. We also anticipate that difficulties in recruitment and adherence of partners may emerge. If this happens, we will consider excluding dyadic analysis but maintaining the analysis of interpersonal variables only.

### Data management {19}

To ensure data protection, all online data collected will be protected by password, and only investigators from the research team will be allowed to access the database that will be saved in an encrypted manner. To ensure confidentiality, all IPs saved will be deleted. Personal identification data will not be saved together with data collection online, as each participant will have a generated code.

### Confidentiality {27}

There will be an individual log-in for each participant and each partner, which protects the confidentiality of data. Participants will enter the platform with their credentials to access the therapy modules, as well as the questionnaires that are requested throughout the study. Partners also need to log in to the platform (with their individual credentials) to answer the questionnaires needed; however, they will not have access to the intervention modules.

### Plans for collection, laboratory evaluation, and storage of biological specimens for genetic or molecular analysis in this trial/future use {33}

Not applicable.

## Statistical methods

### Statistical methods for primary and secondary outcomes {20a}

Descriptive statistics will be reported using means and standard deviations for continuous variables, and frequencies for categorical variables. Primary analyses will follow the intention-to-treat principle. To assess treatment effects, we will conduct analyses of covariance (ANCOVA) comparing post-intervention scores between the experimental and control groups, while adjusting for baseline levels of the respective outcome variable (e.g., LSAS for social anxiety), as well as for age and relationship duration, which will be included as covariates due to their known associations with treatment outcomes and interpersonal functioning. This approach allows for greater precision in estimating intervention effects and accounts for potential baseline imbalances. Missing data will be addressed using multiple imputation under the assumption of missing at random (MAR), in line with recommendations from meta-analytic research on dropout in CBT trials [29]. A two-tailed significance level of *p* < 0.05 will be used for all hypothesis testing. Effect sizes (Cohen’s *d*) will also be calculated to assess the magnitude of between-group differences, consistent with prior meta-analytic findings on the efficacy of internet-based CBT for social anxiety disorder [30].

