### Primary outcomes

Social anxiety symptoms:
Liebowitz Social Anxiety Scale for Adults (LSAS) [21] has 24 items, responded in a 4-point scale. Each item is rated regarding anxiety and avoidance, and so the total score of the scale ranges between 0 and 144, with higher scores indicating higher levels of social anxiety (i.e., below 40 – no discomfort; 40–55 – Mild social discomfort; 55–65 – Moderate social phobia; 65–80 – Marked social phobia; 80–95 – Severe social phobia; Above 95 – Very severe social phobia).Social Phobia Inventory (SPIN) [22] is composed by three subscales: fear, avoidance, and physical discomfort. It contains 17 items in total (16 in the Portuguese version), assessing the symptoms corresponding to these domains. The scale is responded on a 4-point scale, and total score is between 0 and 68, with higher scores indicating higher levels of social anxiety.

Relationship satisfaction:
Global Measure of Relationship Satisfaction (GMREL) [23] is constituted by 5 items answered in a 7-point Likert scale. Scores range between 5 (low relationship satisfaction) and 35 (high relationship satisfaction).

Sexual satisfaction:
Global Measure of Sexual Satisfaction (GMSEX) [23] has 5 items responded in a 7-point Likert scale, with total scores ranging from 5 to 25, with higher values indicating greater sexual satisfaction.

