### Sample size {14}

The sample size calculation was based on the primary outcome of social anxiety as measured by the LSAS. To detect a statistically and clinically significant effect of the intervention, we assumed a large effect size (Cohen’s *d* = 0.80), consistent with prior meta-analytic findings on internet-delivered cognitive behavioral therapy (CBT) for social anxiety disorder. For example, Andrews et al. [28] reported a mean effect size of *g* = 0.80 for computerized CBT across anxiety and depression disorders, including social anxiety. Given that Hedges’ *g* and Cohen’s *d* are practically equivalent in larger samples, we considered this value appropriate for our sample size estimation. Based on this effect size and considering the planned analyses (e.g., intention-to-treat approach and ANCOVA for comparing pre- and post-intervention differences), we estimated that a total of 52 participants (26 per group) would be sufficient to achieve 80% power at a 5% significance level. However, to account for expected dropout rates in CBT studies (approximately 26%), we aimed to recruit at least 70 participants (35 per group). Among all primary outcomes considered, the chosen outcome required the largest sample size to detect a clinically meaningful effect and thus was used for this calculation.

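### Four primary measures are each tested at two-sided 0.05 with no success rule, order or correction, so if any one of them can carry the trial the chance of a false primary claim exceeds 5%

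*Protocol article*

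**What the plan says.** The Outcomes {12} section of the protocol article states: "Primary outcomes include social anxiety symptoms and sexual and relationship satisfaction". That makes three domains. The Primary outcomes section then lists four instruments: "Liebowitz Social Anxiety Scale for Adults (LSAS) [21] has 24 items" and "Social Phobia Inventory (SPIN) [22] is composed by three subscales" for social anxiety, "Global Measure of Relationship Satisfaction (GMREL) [23] is constituted by 5 items" for relationship satisfaction, and "Global Measure of Sexual Satisfaction (GMSEX) [23] has 5 items" for sexual satisfaction.

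The section on statistical methods {20a} plans an ANCOVA of post-intervention scores, adjusted for the baseline of the outcome being analysed, with LSAS given as the example for social anxiety. On the level it is explicit: a two-tailed 0.05 "will be used for all hypothesis testing".

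The Sample size {14} section says: "The sample size calculation was based on the primary outcome of social anxiety as measured by the LSAS". It assumes d = 0.80, 80% power and a 5% level, which gives 26 per group (52 in total), raised to 70 for about 26% dropout. It closes by saying that, of the several primary outcomes, the chosen one needed the largest sample.

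No section says whether success means one primary, all of them, or a particular one. None gives an order of testing, a split of alpha or a correction.

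**The concern.** A protocol article may leave multiplicity details to an analysis plan, and silence alone would not be a finding. This article is not silent. It fixes an uncorrected 0.05 for every test, so a later plan that added a correction would contradict it.

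Followed as written, a trial with no effect on anything has up to four chances to produce a significant primary result, and nothing fixed in advance says which of them would count. LSAS and SPIN are two chances at the same claim. The 5% level then describes each single test but not a conclusion drawn from whichever test succeeded.

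Two features raise the stakes. The section on blinding {17a} says the analysts also support participants and cannot be blinded, and it relies on prespecified hypotheses and outcomes as the safeguard. That safeguard is weak while the primaries are interchangeable. Consequences also hang on the result: controls are offered treatment if there is preliminary efficacy {6b}, and full access to the protocol depends on a reduction in anxiety symptoms {31c}. Neither section names the measure that decides.

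**Working it through.** **Inputs from the protocol article.** Two-sided alpha of 0.05 per test {20a}; four primary instruments in three domains (Outcomes {12} and Primary outcomes); d = 0.80, 26 per group, 80% power, 26% dropout, 70 recruited {14}; 1:1 allocation {16a}.

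**Inputs that are assumptions.** The document gives no correlation between measures. The background section says only, in words, that relationship and sexual satisfaction are strongly related. Assumed here: LSAS-SPIN 0.6-0.8, GMREL-GMSEX 0.5-0.7, and 0.2-0.4 between the anxiety and satisfaction measures.

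**Step 1: the plan's own figure.** For a two-sample t-test with d = 0.80, two-sided 0.05 and 80% power, the solution is 25.5, so 26 per group. At 26 per group the noncentrality is 0.80 × √(26/2) = 2.88 on 50 degrees of freedom, and power is 80.7%. The stated 52 is reproduced. For dropout, 52/0.74 = 70.3, which agrees with the stated 70 to within one participant. The sample size therefore rests on a single test at 0.05.

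**Step 2: error rate if any one primary suffices and every null is true.** For k independent tests the rate is 1 − 0.95^k:

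- k = 4: 1 − 0.8145 = 18.5%
- k = 3: 1 − 0.8574 = 14.3%
- k = 2: 1 − 0.9025 = 9.75%

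For correlated tests, multivariate normal z statistics were simulated and the share of draws with at least one |z| > 1.96 was counted:

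| Tests counted | Correlations assumed | Chance of at least one false positive |
|---|---|---|
| LSAS, SPIN, GMREL, GMSEX | all zero | 18.5% |
| same four | 0.6 / 0.5 / 0.2 (LSAS-SPIN / GMREL-GMSEX / between domains) | 16.8% |
| same four | 0.8 / 0.7 / 0.4 | 14.6% |
| same four | common 0.7 | 13.1% |
| same four | common 0.9 | 9.4% |
| LSAS, GMREL, GMSEX | all zero | 14.3% |
| same three | GMREL-GMSEX 0.5-0.7, between domains 0.2-0.4 | 12.3-13.4% |
| LSAS or SPIN (anxiety claim only) | 0.6-0.8 | 7.8-8.8% |

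Every row exceeds 5%. Partner-reported, weekly and 6-month results are not counted.

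**Step 3: cost of an even split.** Bonferroni over four measures gives 0.05/4 = 0.0125 each. At 26 per group and d = 0.80, LSAS power falls from 80.7% to 61.7% (unadjusted t-test). Restoring 80% would need 37 per group, 74 evaluable, or 74/0.74 = 100 recruited.

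**Step 4: LSAS as gate.** LSAS keeps alpha 0.05, so step 1 is unchanged. If LSAS has no effect, any false claim first needs a false LSAS result, so the rate is at most 5%. If LSAS has an effect, Holm or a fixed order across GMREL and GMSEX holds their joint error at 5%.

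**The case against.** Several objections carry weight.

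*The size depends on assumptions.* A reader might infer that this trial has a 15-19% false-positive rate. The documents do not support that as a fact. The top of that range needs independence, which sits badly with the article's own description of the two satisfaction constructs and with LSAS and SPIN measuring one construct. It also needs four tests rather than three. Where the text names a measure for sizing or analysing anxiety, it names only LSAS. This objection stands, and the figures are given as conditional for that reason.

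*No rule says that any one primary is enough.* This is also true. Three distinct claims, each reported separately at 5%, have a 5% error rate per claim. But the article does not declare separate claims either, and that reading does not cover LSAS and SPIN as two routes to one claim.

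*The sections do not conflict.* A reader might infer that the sample size section makes LSAS the sole primary and that the analysis section contradicts it. It does not: the sample size section itself speaks of several primaries and uses LSAS for sizing. The gap is a missing decision rule, not a contradiction.

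*The aim is described as preliminary efficacy* (Interim analyses {21b}). The Objectives section nevertheless sets out to test efficacy, and the sample size is a conventional calculation at 80% power and 5% level. If the trial is exploratory, the article should say so rather than present several primary tests at 0.05.

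*Putting the satisfaction outcomes behind LSAS changes their standing.* They are a stated purpose of the trial and its novelty. This is a real cost of the fix. The text also gives no basis for ranking GMREL above GMSEX.

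**Conclusion.** The concern holds in conditional form. The article fixes an uncorrected 0.05 for every test across four primary measures and gives no rule for what counts as success. If any one significant measure counts and no effect exists, the false-claim rate is 18.5% with independence and about 15-17% at the assumed correlations. It would be lower with stronger correlations (about 9-13% if all four correlate at 0.7-0.9). It is about 12-14% for three domains with LSAS for anxiety, and about 8-9% for the anxiety claim if either scale suffices. The excess over 5% does not depend on which of these readings is chosen, but its size does. It should be settled before recruitment, because a success rule is credible only if it is set before data are seen.

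**What to change.** In the Outcomes and Primary outcomes sections and in statistical methods {20a}:

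1. Name LSAS at post-treatment as the lead primary test, at two-sided 0.05. This keeps the stated 80% power and the 52 evaluable and 70 recruited participants.
2. Move SPIN to secondary or supportive.
3. Test GMREL and GMSEX only if LSAS is significant. Use either Holm across the two (smaller p-value against 0.025, then the other against 0.05) or a fixed order that the sponsor chooses before recruitment.
4. Replace the blanket 0.05 statement with this rule and treat all other p-values as descriptive.

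The cost is a change of wording and a registry update, with no extra participants. The Trial status section says recruitment had not begun, so there is time. The downside falls on the satisfaction outcomes: claims about them become conditional on LSAS, and under Holm they also face a stricter threshold. A sponsor who wants those claims to stand independently of LSAS could split alpha instead, but an even four-way split cuts LSAS power to 62% at 26 per group, or requires about 100 recruited to restore 80%.
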